### Who will take informed consent (Spirit 26a)

Written informed consent will be obtained from index participants at Visit 1 by a member of the study team and from whānau/household participants at Visit 2 (Figure 1). Assent and parental/caregiver consent will be collected from household/whānau participants who are aged less than 16 years. However, if a 14- or 15-year-old child demonstrates an understanding of what the study involves at Visit 2, they will be invited to complete consent. Additional written consent will be requested from index participants at visit 1 for several sub-studies. These include (1) participation in a mixed meal tolerance test at two timepoints (2) participation in a sub-study around the measurement of dietary intake using a phone application. In addition, at visit 1, index participants will be asked if they wish to learn more about a qualitative study that runs in parallel with the current study. If so, their contact details will be passed to a qualitative researcher who will contact them by phone with further details and will take consent, as applicable.

### Additional consent provisions for collection and use of participant data and biological specimens (Spirit 26b)

Participants will be given the option to provide written consent for their blood samples and related meta-data to be included in an anonymous manner in a biobank.

### Intervention for RCT 1 (Spirit 6b and 11a)

The two arms in RCT 1 are: (a) the intervention arm, which is a package that includes food provision designed to supply the majority of estimated energy requirements for participants, combined with recipes, weekly meal plans, access to web-based nutrition education and opt-in online social support; and (b) the control arm, which is usual dietary intake and lifestyle, i.e., usual care.

The food provision will comprise food delivery to the participants’ homes for 12 weeks and is provided free of charge. The food will be assembled and delivered by two commercial companies, one of which is a meal kit home delivery service and the other is a grocery provider. The meal kit home delivery service will deliver food and recipes for five evening meals and fruit, and the grocery provider will deliver food that can be used for breakfast, lunch and snacks.

The food from both companies will be predominantly plant-based and rich in fruit and vegetables, grains, legumes, seafood, nuts, with some meat and dairy. The five New Zealand food groups used as the basis of the food provision are: vegetables; fruit; grain foods; legumes, nuts, seeds, fish and other seafood, eggs, poultry or red meat with fat removed; and reduced-fat milk and milk products. The amount of food provided is designed to provide approximately 75% of estimated energy requirements for the index participant and up to five members of their household/whānau. The food provided will align with a Mediterranean dietary pattern and when combined with the remaining ~25% energy requirements provided by participants themselves, will aim to fall within the acceptable total energy and macronutrient reference ranges for fat, carbohydrate and protein (32). Further details on the estimated energy, macronutrient distribution and food provided will be published separately. If a participant and their household/whānau go on holiday during the 12-week intervention period, the food delivery will be temporarily paused and will resume when they return home. During this time, they will be encouraged to adhere to the dietary pattern and will continue to have access to the education and social support resources.

The meal kit home delivery service and the grocery provider deliver food that has come from two sources; food provided in-kind to the study by New Zealand food and beverage (F&B) companies and food that is purchased by the research team. The food provided in-kind will be transported from the F&B companies directly to the meal kit home delivery service and the grocery provider, and then distributed to study participants. The involvement of the F&B companies was such that a nationwide call was made by the funding body (High Value Nutrition National Science Challenge) to F&B companies in New Zealand who wished to partner in the research study. The researchers assessed whether their foods align with the dietary pattern and if so, agreed on the quantity of food to be provided. The F&B companies had no direct role in the design or composition of the dietary pattern. Regular communication will take place between the researchers and the F&B companies who provide food.

The meal kit home delivery service will deliver meals that will have been pre-selected on behalf of the participants by a study dietitian. These meals will be either vegetarian, fish-based, or contain lean meat wherever possible. There are three grocery boxes that will be provided weekly by the grocery provider which have been developed by the research team to align with weekly breakfast, lunch and snack suggestions and recipes. These will be rotated over three weeks to provide variety, with each box being provided four times over the 12-weeks. An additional ‘Starter Box’ of products will be provided at the beginning of the 12-week period. The ‘Starter Box’ will include items that participants can use either immediately or throughout the entire 12-week period such as macadamia nuts, dried fruit, fish oil dressing, honey and seaweed snacks. Examples of the items in the other three boxes that are provided in a rotating manner are breakfast cereal, reduced-fat milk, seeds, rice cakes, olive oil, tuna, nuts, beans, lentils and fruit. The menu plans and recipes will be accessible through the study website.

The implementation of the dietary intervention incorporates elements of behavior change science which will be delivered by a multidisciplinary team including trained research staff and allied health care professionals including dietitians. Each site will have one research assistant and a doctoral student to support the clinic visits and arrange for the provision of food. The site staff will also make participants aware of the website and social media support options available to them and will play the website video titled “Introduction to the diet” so participants will be aware of what the dietary pattern entails. The behavioral aspects of the trial aim to support adherence to the NZMedDiet pattern and will include private Facebook groups and Facebook Messenger chats with a dietitian and peer support (online social support) which will be managed by one doctoral student who is a registered dietitian; a behavior change contract signed by participants prior to beginning RCT 1; and educational and motivational resources hosted on a participant facing website and YouTube channel. The website will be developed prior to the trial starting and will have six tabs covering: 1. Research Team, 2. Industry partners, 3. Nutrition support 4. Industry products, 5. Participant frequently asked questions and 6. Contact Us. The Nutrition Support section will link to short videos which will cover an introduction to the diet, goal setting, sample menus and recipes. The Nutrition support will also include multiple one-minute videos recorded by members of the research team, such as those entitled “Planning your shopping,” “Meal Planning,” “Getting to know your ingredients,” “Cooking” and “What to do with leftover food/ kai,” “Understanding your health data,” “Keeping motivated” and “Healthy Holiday Tips.” The behavior change wheel was used to design these resources to overcome identified barriers to the behavior, such as time and cost (17, 18). The participants will be able to interact with the website and online social support as little or as much as they chose.

### Control arm for RCT 1; usual dietary intake and lifestyle

Participants allocated to the control arm will continue their usual lifestyle and diet for 12-weeks. Nutritional education and social support will not be provided. At the end of this 12-week period, they will receive the intervention package described above, for 12-weeks.

### Intervention for RCT 2 (Spirit 6b and 11a)

At the end of the 12-weeks of RCT 1, participants randomized to the RCT 1 intervention will immediately be randomized to continuing the opt-in online social support or stopping it. Participants randomized initially to the RCT 1 control will then receive the RCT 1 intervention package described above for 12-weeks and will then be randomized to RCT 2 to either continuing the opt-in online social support or stopping it (Figure 1). All participants will continue to have access to the bespoke study website housing nutrition information.

### Criteria for discontinuing or modifying allocated interventions (Spirit 11b)

Enrolled participants from either arm can withdraw from the study at any time during the study. The reason for withdrawal will be captured.

### Strategies to improve adherence to the intervention (Spirit 11c)

Ongoing support will be provided by a member of the research team which includes the development and provision of additional short videos for the study website containing strategies around adhering to the intervention during holiday periods such as Christmas and New Year. Participants will also receive ongoing bespoke individualized support from the same team member in response to barriers they may encounter and queries they may have. Measurements and outcomes (Spirit 12).

### Outcomes for RCT1 and RCT2

The primary outcome for RCT 1 and RCT 2 is MetSSS in index participants. Secondary outcome measures for RCT 1 and RCT 2 for index and household/whānau participants are listed in Table 4. The behavior change elements of the trial are designed to support adherence to the dietary intervention and will be assessed using the Food Frequency Questionnaire (FFQ) and the Mediterranean adherence diet score which is taken from the FFQ data. While online engagement metrics as count scores will be assessed, these have little to no clinical relevance and will be used as modifying factors in the analysis.

**Table 4 tab4:** Primary and secondary outcome measures for RCT1, RCT2 and the longitudinal cohort study for index participants and for household/whānau members.

Outcome variables	RCT 1	RCT 2	LCS	Proposed analysis
Primary outcome				
MetSSS	X	X	X	ANCOVA with baseline measurements as covariate, see text for details of sensitivity analysis confounders and sub-group
Secondary outcomes				
Weight	X	X	X	ANCOVA with baseline measurements as covariate
Body mass index	X	X	X	ANCOVA with baseline measurements as covariate, consideration of logarithm transformation
Lean mass (FFM calculated from BIA and DXA measurements)	X	X	X	ANCOVA with baseline measurements as covariate
Fat mass (calculated from BIA and DXA Measurements)	X	X	X	ANCOVA with baseline measurements as covariate
Dietary pattern measured using Food Frequency Questionnaire	X	X	X	
Individual components of MetSSS				
Glucose	X	X	X	ANCOVA with baseline measurements as covariate
Triglycerides	X	X	X	ANCOVA with baseline measurements as covariate, consideration of logarithm transformation
HDL cholesterol	X	X	X	ANCOVA with baseline measurements as covariate
Systolic blood pressure	X	X	X	ANCOVA with baseline measurements as covariate
Waist circumference	X	X	X	ANCOVA with baseline measurements as covariate
HbA1c	X	X	X	ANCOVA with baseline measurements as covariate
Insulin	X	X	X	ANCOVA with baseline measurements as covariate, consideration of logarithm transformation
HOMA	X	X	X	ANCOVA with baseline measurements as covariate, consideration of logarithm transformation
Total cholesterol	X	X	X	ANCOVA with baseline measurements as covariate
LDL cholesterol	X	X	X	ANCOVA with baseline measurements as covariate
Diastolic BP	X	X	X	ANCOVA with baseline measurements as covariate
hsCRP	X	X	X	Mann–Whitney test with Hodges Lehmann estimator
Quality of life				
SF36 (MCS and PCS and all dimensions)	X	X	X	ANCOVA with baseline measurements as covariate
Kaupapa Māori Wellbeing questionnaire	X	X	X	Analyzed and reported separately
Online engagement metrics	X	X		*Count scores*
Self-evaluation COM Questionnaire	X	X	X	*Count scores*
Impact evaluation	X	X	X	*Qualitative thematic analysis*

LCS, longitudinal cohort study; MetSSS, metabolic syndrome severity score; FFM, fat free mass; BIA, bioelectrical impedance; DXA, dual-energy X-ray absorptiometry; HDL, high density lipoprotein; HOMA, homeostatic model assessment; LDL, low density lipoprotein; hsCRP, high sensitivity C reactive protein; MCS, mental component summary; PCS, physical component summary.

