### Trial design (Spirit 8)

This is a multi-center, three-stage trial, with two randomized controlled trials (RCTs); both parallel group superiority trials, and a longitudinal cohort study. The first RCT (RCT 1) compares the effect of Mediterranean dietary pattern incorporating high quality New Zealand foods (NZMedDiet pattern) to usual diet on MetSSS, a marker of cardiometabolic health for 12-weeks. The intervention in RCT 1 includes elements of behavior change science including the provision of food, recipes, weekly meal plans, access to web-based nutrition education and opt-in online social support. From here on within the manuscript ‘RCT 1 intervention’ is referred to as a package including these described aspects. The second RCT (RCT 2) compares the opt-in online social support, to no online social support with an outcome assessment 12 weeks after the second randomization (Figure 1). Those participants who were originally randomized to the control group in RCT 1 will be given the RCT 1 intervention before the second randomization. After the second randomization, both groups continue to have access to the bespoke study website housing nutrition information and education. The third stage is a longitudinal cohort study where all participants are followed for 12 months from the start of the dietary intervention. The trial design is summarized in Figure 1 (Spirit 8).

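### Online engagement counts cannot serve as effect modifiers in RCT 1, nor in RCT 2 when measured after the second randomisation; only engagement before that randomisation can

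*Protocol article*

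**What the plan says.** The section Outcomes for RCT1 and RCT2 states that engagement will be assessed as count scores and that "these have little to no clinical relevance and will be used as modifying factors in the analysis". The heading covers both trials, and no metric, time window or model is named. Table 4 lists "Online engagement metrics" for RCT 1 and RCT 2 but not for the cohort stage, and its analysis column says only that they are count scores.

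Four other statements determine what these counts can be:

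- RCT 1 control arm: "Nutritional education and social support will not be provided".
- RCT 1 intervention arm: "The participants will be able to interact with the website and online social support as little or as much as they chose".
- RCT 2: participants are "randomized to RCT 2 to either continuing the opt-in online social support or stopping it", while "both groups continue to have access to the bespoke study website housing nutrition information and education" (Trial design).
- Before RCT 2 everyone has had the package: "Those participants who were originally randomized to the control group in RCT 1 will be given the RCT 1 intervention before the second randomization" (Trial design).

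The Statistical analyses section lists the variables for treatment-by-subgroup interaction: age, sex, starting diet score, size of the household and presence of children. Engagement is not among them. The section leaves possible other modifiers to the statistical analysis plan.

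**The concern.** An effect modifier should be a characteristic that exists in both arms and is not itself a result of allocation. The five listed subgroup variables can all be fixed before randomisation. Engagement in RCT 1 meets neither condition: it starts after allocation, and only one arm has anything to engage with. An interaction model would then either fail or, once the software drops the redundant column, return the slope of outcome on engagement among people who chose how much to engage. Motivated participants may both log in more and improve more for other reasons, so that slope does not show that engagement changes the effect of treatment.

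The stakes are greater in RCT 2, whose randomised question is whether continued social support helps. An engagement association there could be taken as evidence on that question although it is not a randomised comparison.

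**Working it through.** The protocol gives no figure for the engagement analysis, so there is none to reproduce. The check has two parts: identifiability, which needs no assumed values, and the size of a spurious association, which does.

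**1. Identifiability.** Write T for allocation (0 or 1), B for baseline MetSSS and E for the engagement count. The interaction model has five columns: 1, B, T, E and T×E.

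- *RCT 1, E = 0 in controls.* If T = 0, then E = 0 and T×E = 0. If T = 1, then T×E = E. So T×E = E for everyone, two columns coincide, and the rank is 4 of 5. The interaction is not identifiable.
- *RCT 1, E undefined in controls.* If controls are set to missing they leave the analysis, T is 1 throughout, T equals the intercept and T×E equals E. The rank is 3 of 5 and no treatment contrast is left.
- *RCT 2, social-support counts after the second randomisation.* The stop arm has E = 0 by design, as RCT 1 controls do: rank 4 of 5.
- *RCT 2, website counts after the second randomisation.* Both arms keep the website, so E varies in both: rank 5 of 5. The model can be fitted, but E may respond to allocation and share causes with the outcome.
- *RCT 2, engagement during the package before the second randomisation.* Everyone has received the package: rank 5 of 5, and E is a baseline variable for RCT 2. The section on allocation sequence adds that participants learn their RCT 2 arm only after completing the package, so knowledge of that arm cannot shape this count.

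**2. Size of a spurious association (assumed values).** Suppose engagement has no effect and only marks motivation. Let motivation shift the outcome by b standard deviations and correlate ρ with engagement. Within one arm of n = 100 (half of 200), the induced correlation is r = ρb/√(1+b²), the expected test statistic is about r√n/√(1−r²), and the rejection rate is approximately the probability that it exceeds 1.98 in absolute value.

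| b | ρ | r | expected statistic | rejection rate |
|---|---|---|---|---|
| 0.10 | 0.3 | 0.030 | 0.30 | 6% |
| 0.10 | 0.9 | 0.090 | 0.90 | 14% |
| 0.25 | 0.3 | 0.073 | 0.73 | 11% |
| 0.25 | 0.5 | 0.121 | 1.22 | 22% |
| 0.25 | 0.7 | 0.170 | 1.72 | 40% |
| 0.25 | 0.9 | 0.218 | 2.24 | 60% |

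Direct simulation of the same set-up agrees to within one or two percentage points.

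A stronger scenario was simulated with the protocol's 184 participants (92 per arm, 4,000 runs): a true effect of −0.40 in everyone, no modification, a motivation effect of −0.3 against a residual standard deviation of 0.6, and engagement Poisson with mean exp(1 + 0.6 × motivation). With engagement present only in the treated arm, its slope was significant in 86% of runs and averaged −0.076. The treatment coefficient averaged −0.15. That coefficient is now the contrast at zero engagement. Mean engagement is exp(1 + 0.6²/2) = 3.25, and −0.152 − 0.076 × 3.25 ≈ −0.40 recovers the true effect. When engagement was instead measured before randomisation in both arms, the treatment coefficient averaged −0.40 and the interaction was falsely significant in 6% of runs, close to the nominal 5%.

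**The case against.** The strongest reply is that the protocol commits to no particular model. It gives no metric or window, leaves engagement out of its interaction list, and defers other modifiers to an analysis plan that is not shown. A sensible plan could use pre-RCT 2 engagement and meet the point entirely. This stands in part: a reader should not say that the protocol prescribes a singular model. But the statement that engagement will be used as a modifying factor is unconditional and covers both trials, and the deferral of other modifiers does not withdraw it. For RCT 1 no choice of window within the trial rescues it.

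Several stronger readings are tempting, and the documents do not support them:

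- *Engagement exists only in the supported arm throughout, so no interaction can be estimated.* Not so in RCT 2. Both arms keep the website, and everyone has a package period before the second randomisation.
- *Table 4 plans a between-arm test of engagement.* The table gives only count scores, whereas other rows name ANCOVA or Mann–Whitney. No such test is stated.
- *The trial would report that support works in those who use it even when it does nothing.* That depends on how the result is presented, which the protocol does not say.
- *A single false-positive rate can be quoted.* It cannot. The rate moves with the assumed motivation effect and its correlation with engagement, and the protocol gives neither.

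**Conclusion.** The point holds in limited form. In RCT 1, and in RCT 2 for social-support counts after the second randomisation, a treatment-by-engagement interaction is not identifiable (rank 4 of 5). This follows from the design and assumes only that participants without the support have no counts. Website counts after the second randomisation are estimable in RCT 2 but remain post-randomisation and open to bias. Of the definitions examined, only engagement before the second randomisation gives a sound modifier.

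Under the assumed values, a spurious engagement association appeared in about 6% to 86% of cases. The range illustrates the risk and is not a forecast. The primary ANCOVA contains only baseline MetSSS and allocation, so the primary result is unaffected. This is a secondary-analysis matter that should be corrected before the data are analysed.

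**What to change.** In Outcomes for RCT1 and RCT2, and in the analysis plan:

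1. State that engagement measured during a randomised period will not be used as an effect modifier in either trial. Report it descriptively as a process or adherence measure, and label it so in Table 4.
2. If modification by engagement is wanted, confine it to RCT 2. Define the modifier as engagement during the 12-week package before the second randomisation, name the metric (social support, website or both), and add it to the interaction list in Statistical analyses.
3. Confirm that counts are logged for the original controls during their delayed package, weeks 12 to 24 in Table 5. Table 4 marks engagement only for RCT 1 and RCT 2, and no section says that it is recorded in that window.
4. If an effect of actual use is of interest, a complier-average analysis with allocation as instrument should be confined to RCT 2. In RCT 1 allocation also delivers food meant to cover about 75% of energy needs, so it can affect MetSSS by routes other than engagement and the exclusion restriction fails. In RCT 2 that restriction is still an assumption to be stated, since participants know their arm.

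The cost is wording, plus a check of the logging set-up. No change to sample size, visits or the primary analysis is needed. If counts for the delayed package are not being captured, capture has to be switched on or the modifier analysis dropped.

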#### Outcomes for longitudinal cohort study

The primary outcome measure for the longitudinal cohort study is MetSSS in index participants 52 weeks after the start of the RCT 1 intervention package, whether that be at the beginning of the trial for those randomized to this arm initially, or after the initial 12-week control period for those randomized to the usual care arm of RCT 1. Secondary outcome measures for index and household/whānau participants are also listed in Table 4.

